#### Focus Groups

We will conduct 12 focus groups in study 1. Focus groups, a standard tool in market research, have been employed by health researchers to obtain qualitative information for developing and testing various interventions and messages [78]. Focus groups are used to obtain in-depth information regarding awareness, feelings, attitudes, beliefs, fears, experiences, values, needs and reactions regarding issues or products.

##### Participants

Twelve focus groups, each comprised of 8-12 unacquainted individuals, will be conducted. Focus groups will be conducted with American Indian/Alaskan Native women and will be stratified by residential location of participants (e.g., rural or reservation vs. urban). Participants will include women who are 40 years of age and older (in concordance with the American Cancer Society's recommended beginning age for annual screening of asymptomatic women) and will be further stratified by age (e.g., 40-64 year-olds and those aged 65 years and older). All participants will have had at least one mammogram performed within the past five years.

Focus group participants will be recruited at an Indian Health Service clinic through referral from clinic personnel and through posters in the waiting area. Participants who do not use the above-mentioned health service clinic may be more difficult to reach because there is no central location through which to reach them. We will post flyers and posters at various community locations in the four primary Kansas Indian Reservation sites located in Horton (Kickapoo), White Cloud (Iowa Tribe of Kansas and Nebraska), Mayetta (Prairie Band Potawatomi Nation), and Reserve (Sac and Fox Nation) Kansas. We will also post flyers at other local AI/AN venues including the Heart of America Indian Center and the offices of the American Indian Council. A brief questionnaire at the time of recruitment will allow us to assign groups based on the sampling frame illustrated in Table 2.

**Table 2 T2:** Focus Group Sampling Frame

AI/AN Women			
**Age 40-64**		**Age 65+**	

**Rural/Reservation**	**Urban**	**Rural/Reservation**	**Urban**

3 groups	3 groups	3 groups	3 groups

36 participants	36 participants	36 participants	36 participants

Focus group moderator's guides will be developed with input from program advisory board members and will be based partially on information from our prior mammography focus groups with Non-Hispanic White, Hispanic, and Black women. Discussions will focus on barriers to obtaining mammograms, motivating factors to obtain mammograms, past mammography experiences, and areas of mammography satisfaction and dissatisfaction.

##### Conduct

Focus group meeting times will be two hours and all groups will be audio- and videotaped. We understand that effective use of the focus group requires development of insightful, appropriate questioning frameworks and outlines for the group moderator. As a result, an American Indian moderator, informed of the study goals and operating with a prepared outline, will facilitate and elicit responses from participants. The moderator will take steps to create a nonthreatening, nonjudgmental, supportive climate conducive to open exchange and expression, ensure that the session direction remains relevant to the study, ensure that all group members are allowed to contribute, and ensure that responses are not inhibited or shaped by one or two dominant members. Prior to the start of the focus group, all participants will provide both written and verbal informed consent and then complete a brief demographic survey. Any person who does not wish to consent will not be eligible for participation. Participants in the focus groups will be reimbursed $25.00 for their time and transportation. We will also provide a light meal for all focus group participants.

##### Mammography Satisfaction Focus Groups with Hispanic, White, and Black Women Conducted Previously

We will pair the AI/AN focus group information ascertained within this project with transcripts from [name] prior focus group study with Non-Hispanic White, Hispanic, and Black women [79]. In brief, however, [name] conducted focus groups with over 100 women to identify issues related to mammography satisfaction. These groups were held in rural and urban communities and were conducted with African American, Hispanic, and Non-Hispanic white women. Focus group participants identified five major themes that contributed to satisfaction with their mammography experiences: 1) scheduling appointments, 2) mammography exam discomfort/pain, 3) mammography facility environment, 4) treatment by the mammography technologist, and 5) reporting of mammography results. Further analyses have also been conducted to assess differences between racial/ethnic focus group participants. These analyses found pain and waiting room time to be issues that primarily affected African American women. Hispanic women largely experienced embarrassment and fatalistic beliefs during mammograms. White women were most affected by instructions that either prepared them for the exam or were given during the exam. The transcripts from these focus groups conducted for another study will be re-examined according to the current study rubric described above. The availability of these transcripts and pairing of them with the current study focus group transcripts will allow for a rich assessment of the variations in mammography experiences and satisfaction between women belonging to four very distinct racial/ethnic groups and shed particular light onto the mammography service issues that are of particular importance to each population group. These data will provide necessary insight into areas of mammography service that may be tailored to women from differing racial/ethnic background to enhance their mammogram experience.

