## Study Aims and Hypotheses

### Aims and Hypotheses

**Aim #1: **To compare the mammography experiences and satisfaction with mammography services of Native American/Alaska Native women with that of Non-Hispanic White, Hispanic, and Black women.

**Hypothesis**: There will be significant and describable variation in women's experiences and satisfaction with mammography experiences between American/Alaska Native, Non-Hispanic White, Hispanic, and Black women.

**Aim #2: **To develop and validate the psychometric properties of an American Indian Mammography Satisfaction survey.

**Aim #3: **To assess variation among American Indian/Alaskan Native women's assessments of their mammography experiences and mammography service satisfaction.

**Hypothesis**: There will be significant variation in satisfaction with mammography experiences between women receiving mammography services within the Indian Health Service system vs. those receiving services outside of the Indian Health Service system.

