##### Qualitative Data Analysis

Transcribed audiotapes will be coded and analyzed using ATLAS ti, a qualitative data analysis program. The coding protocol will be developed using a combination of several qualitative analysis approaches. Initially transcriptions will be "open coded": identifying within the text key words, themes, and descriptions of behavior [80]. Subsequently, we will group these themes into coding categories and develop a code map. This will allow us to categorize and retrieve issues related to patient satisfaction, barriers to obtaining mammograms, mammogram preferences, and culturally-specific issues related to obtaining mammograms. Key ideas, words, phrases, and recommendations will be examined to formulate summary statements and conclusions. For core coding categories, two independent observers will code data. We plan separate analyses for each stratum to see if differences emerge. In addition to text analysis, we will develop ethnographic decision models (EDMs) for each stratum. EDMs are causal models that predict the types of choices people will make under certain circumstances [77]. They have been used in anthropology for many purposes, including the way people decide which treatment to use. In this case, EDMs will consist of decisions a woman must make to decide if she will have a mammogram. EDMs will be evaluated to develop a comprehensive EDM for the population which will help develop an effective intervention to increase mammography rates in AI/AN women.

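### In Aim 1 every AI/AN-versus-other contrast is also a new-study-versus-earlier-study contrast, and recoding the old transcripts cannot tell a topic not asked from a topic not an issue

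*Protocol article*

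**What the plan says.** Aim 1, under Aims and Hypotheses, is "To compare the mammography experiences and satisfaction with mammography services of Native American/Alaska Native women with that of Non-Hispanic White, Hispanic, and Black women". Its hypothesis is "There will be significant and describable variation in women's experiences and satisfaction with mammography experiences" across the four groups.

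The twelve focus groups of Study 1 are all with AI/AN women aged 40 or over who had a mammogram in the past five years (Participants). Their topics are given as: "Discussions will focus on barriers to obtaining mammograms, motivating factors to obtain mammograms, past mammography experiences, and areas of mammography satisfaction and dissatisfaction". The moderator's guides take advisory board input and "will be based partially on information from our prior mammography focus groups with Non-Hispanic White, Hispanic, and Black women".

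Data on the other three groups come from a prior project that "conducted focus groups with over 100 women to identify issues related to mammography satisfaction" (Mammography Satisfaction Focus Groups with Hispanic, White, and Black Women Conducted Previously). That section states the harmonising step: "The transcripts from these focus groups conducted for another study will be re-examined according to the current study rubric described above". It then says that pairing the two sets will show how experiences and satisfaction vary between the four racial/ethnic groups and will inform tailoring of services to each.

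Under Qualitative Data Analysis, the code map is to retrieve issues related to "patient satisfaction, barriers to obtaining mammograms, mammogram preferences, and culturally-specific issues related to obtaining mammograms".

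**The concern.** Focus-group text depends on what the moderator raises. When one population is questioned in one study and its comparators in another, with a different stated purpose, a theme may be missing from the comparator transcripts for either of two reasons: the women did not see it as an issue, or nobody brought it up. The plan applies a common coding scheme to both sets and reads the differences as variation between racial/ethnic groups.

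The interpretation of Aim 1 is at stake. The article draws the racial/ethnic inference without qualification and intends to act on it in tailoring services. Both sets of transcripts also feed the content of the AIMS survey in Study 2. The IHS versus non-IHS comparison in Aim 3 does not depend on this contrast.

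**Working it through.** There is no figure to reproduce. The only sample size calculation belongs to Aim 3. The check sets the sections side by side.

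1. **Source of data.** AI/AN: new groups only. White, Hispanic, Black: earlier transcripts only. Four groups give 4 × 3 / 2 = 6 pairwise contrasts. The 3 that involve AI/AN women coincide completely with study. The 3 among White, Hispanic and Black women lie within the earlier study and do not.

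2. **Topics raised.** The new groups have four topics. Against the earlier groups' stated purpose:
   - satisfaction and dissatisfaction: matches;
   - past experiences: overlaps in part, since the five earlier themes are described as contributing to satisfaction with the experience;
   - barriers: not named in that purpose;
   - motivating factors: not named in that purpose.

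   A stated purpose is not a question list, so this shows where elicitation may have differed, not that it did.

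3. **Codes applied.** I take the current rubric to be the coding scheme under Qualitative Data Analysis, although that section follows the sentence that calls it already described. Its categories go beyond satisfaction to barriers, preferences and culturally specific issues. They are to be applied to transcripts whose stated purpose was satisfaction.

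4. **What an empty code means.** If the new guide raises a topic and no text results, the topic was asked about and not taken up. If the old transcripts hold no text under the same code, it was either asked about and not taken up, or not asked. Recoding works on text that exists, so it cannot separate the two.

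5. **Other differences tied to study.** The new groups have "an American Indian moderator, informed of the study goals and operating with a prepared outline"; the article does not describe the earlier moderators. Basing the new guide partly on the earlier groups narrows the gap in topics. It could also lead to AI/AN women being prompted on themes that earlier participants raised themselves, though the text does not say that such prompts are planned.

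6. **Safeguards.** From Participants through Qualitative Data Analysis, nothing limits the comparison to topics common to both studies or marks topics that were not raised. The Discussion does not name the two-study source as a limitation.

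**The case against.** Much of the case on the other side is sound.

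- **The earlier guide and eligibility criteria are not shown.** The guide may have asked about barriers, and the age and mammogram criteria may have been the same. This stands: the extent of unequal questioning cannot be known from the article.
- **Aim 1 names only experiences and satisfaction.** Both studies cover these at least in part. Barriers and motivators have another evident use, in the decision models planned for AI/AN women. This stands as a limit on size. It does not remove the problem, because the old transcripts are to be recoded to a rubric that includes barriers and culturally specific issues.
- **The earlier transcripts are not empty on these matters.** Scheduling, waiting time, embarrassment and fatalistic beliefs are reported from them, and the article's own Access to Mammography section counts ease of appointment and waiting time as access barriers. A forecast that such codes will stay sparse is therefore not supported.
- **Guide and codebook details are commonly left out of an article.** That is fair for details. Here, however, the article itself states both the design and the inference to racial/ethnic variation, without qualification.

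A reader might infer that half of the new guide, two topics of four, will produce AI/AN-only themes by construction. The documents do not support this, because they do not show what the earlier guide asked and Aim 1 does not name those two topics. A reader might also infer that the Aim 1 hypothesis would be borne out even if the populations were identical. That would need unequal elicitation on experiences or satisfaction, which is not shown, and the hypothesis also spans the three contrasts within the earlier study.

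**Conclusion.** The concern holds as a problem of interpretation that should be corrected. The complete overlap of AI/AN status with study follows from the design as written and needs no assumption about the earlier guide. That questioning differed is an inference from the earlier groups' stated purpose and from the only partial link between the guides. Its extent is unknown.

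The risk is greatest for barrier, motivator and culturally specific codes, smaller for experiences and satisfaction, and absent on this account for contrasts among White, Hispanic and Black women. As the plan stands, a topic raised only with AI/AN women can be reported as a racial/ethnic difference.

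**What to change.** In the section on the previously conducted focus groups and in Qualitative Data Analysis:

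- Compare the two moderator guides and limit the Aim 1 AI/AN-versus-other comparison to topics raised in both.
- Code a topic that the earlier guide did not raise as 'not elicited', not as absent.
- Report topics asked only of AI/AN women as description within that group.
- Where the earlier demographic data allow, check the comparison in earlier participants who meet the same age and recent-mammogram criteria.
- Word the Aim 1 hypothesis, and the interpretation of the paired transcripts, as a descriptive comparison across two studies.

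Including the earlier satisfaction questions in the new guide is desirable and has to be settled before the first group meets. Placing them verbatim as an opening block is optional, since it may sit poorly with inductive focus-group work.

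The cost is one comparison of guides, a coding rule and some rewording, with no extra groups. The price is a cross-ethnic comparison that covers fewer topics.

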##### Qualitative Data Analysis

Transcribed audiotapes will be coded and analyzed using ATLAS ti, a qualitative data analysis program. The coding protocol will be developed using a combination of several qualitative analysis approaches. Initially transcriptions will be "open coded": identifying within the text key words, themes, and descriptions of behavior [80]. Subsequently, we will group these themes into coding categories and develop a code map. This will allow us to categorize and retrieve issues related to patient satisfaction, barriers to obtaining mammograms, mammogram preferences, and culturally-specific issues related to obtaining mammograms. Key ideas, words, phrases, and recommendations will be examined to formulate summary statements and conclusions. For core coding categories, two independent observers will code data. We plan separate analyses for each stratum to see if differences emerge. In addition to text analysis, we will develop ethnographic decision models (EDMs) for each stratum. EDMs are causal models that predict the types of choices people will make under certain circumstances [77]. They have been used in anthropology for many purposes, including the way people decide which treatment to use. In this case, EDMs will consist of decisions a woman must make to decide if she will have a mammogram. EDMs will be evaluated to develop a comprehensive EDM for the population which will help develop an effective intervention to increase mammography rates in AI/AN women.

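### The decision models claim to cover the whole AI/AN population, but the focus groups contain no never-screened woman and none lapsed for more than five years

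*Protocol article*

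**What the plan says.** Under Qualitative Data Analysis (Study 1), the protocol article adds EDMs to the text analysis, one for each stratum. It describes them in strong terms: "EDMs are causal models that predict the types of choices people will make under certain circumstances". The choice to be modelled is named: "EDMs will consist of decisions a woman must make to decide if she will have a mammogram". The stratum models are then to be evaluated in order to "develop a comprehensive EDM for the population which will help develop an effective intervention to increase mammography rates in AI/AN women".

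The Participants section under Focus Groups settles who supplies the data: "All participants will have had at least one mammogram performed within the past five years". On size it says: "Twelve focus groups, each comprised of 8-12 unacquainted individuals, will be conducted". Table 2 divides the groups by age (40-64, 65 and over) and by residence (rural/reservation, urban). Screening history is not a stratum. The same section sets the agenda: "Discussions will focus on barriers to obtaining mammograms, motivating factors to obtain mammograms, past mammography experiences", together with satisfaction and dissatisfaction.

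The Background gives AI/AN screening rates of 37% within one year and 52% within two years, against a recommendation of yearly mammography from age 40. It gives no five-year rate.

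**The concern.** A model of whether a woman has a mammogram draws its information from women who went and women who did not. Here admission to the sample depends on having gone at least once in five years, so the sample is selected on a version of the outcome that the model is meant to predict. That rule is sensible for studying satisfaction, which needs women with an experience to report. It fits poorly with a causal, predictive model offered for the whole population.

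The EDM is the Study 1 output tied most directly to raising screening rates. If it is read as a population model, an intervention could be built on barriers reported only by women who got past them at least once in five years. Whatever keeps other women from being screened at all would be missing, and nothing in the data would reveal the gap.

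**Working it through.** No sample size or power figure depends on this point, and the plan gives no figure of its own to reproduce. The check sets the two sections side by side and then bounds what is excluded and what variation remains.

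**1. Who can be in the EDM data.** 12 groups × 8 to 12 women = 96 to 144 women; Table 2 shows the upper limit, 4 × 36 = 144. Each stratum has 3 groups, hence 24 to 36 women. Under the eligibility rule, none of them can be never-screened or more than five years lapsed.

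**2. Whether another source supplies those women.** The earlier transcripts come from Non-Hispanic White, Hispanic and Black women and concern satisfaction with mammography. The pilot survey in Study 2 also requires a mammogram within five years (Table 3). Neither supplies never-screened or long-lapsed AI/AN women.

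**3. Share of the population excluded.** Let s be the share of eligible-age AI/AN women screened within five years. It is not given. It cannot be below the two-year rate, so s lies between 0.52 and 1.00. The excluded share is 1 − s, which runs from 1 − 1.00 = 0% to 1 − 0.52 = 48%.

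**4. Variation left among eligible women.** Assume that participants mirror the quoted rates. Among women screened within five years:
- share with none in the last year = (s − 0.37)/s
- share with none in the last two years = (s − 0.52)/s

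| s (assumed) | Excluded, 1 − s | None in last year | None in last two years |
|---|---|---|---|
| 0.52 | 48% | 0.15/0.52 = 28.8% | 0/0.52 = 0% |
| 0.70 | 30% | 0.33/0.70 = 47.1% | 0.18/0.70 = 25.7% |
| 1.00 | 0% | 0.63/1.00 = 63.0% | 0.48/1.00 = 48.0% |

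**5. What that means per stratum.** With a 12-month cut, the low end gives 24 × 0.288 ≈ 7 to 36 × 0.288 ≈ 10 overdue women, and the high end 24 × 0.63 ≈ 15 to 36 × 0.63 ≈ 23. With a 24-month cut, the low end gives none.

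So a mammogram within five years is constant by design, while on-time versus overdue screening, at least at 12 months, is not.

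**The case against.** A reader might infer that the outcome does not vary at all and that the models cannot identify what stops women. The documents do not support that. The article does not define the modelled decision as any mammogram in five years. Screening is recommended yearly, so a woman last screened three or four years ago is eligible and has passed over several screens. Barriers and motivating factors are on the discussion agenda, and such women can say what held them back. The article itself treats low repeat use as a central problem, and a model built on previously screened women bears on it.

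A reader might also take 48% as the share excluded. That is the share without a mammogram in two years, whereas the exclusion is at five. Women last screened two to five years ago belong to the 48% and are eligible. It is an upper bound only.

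Finally, the EDMs supplement the text analysis, no stated aim or hypothesis rests on them, and they only contribute to an intervention still to be developed. A condensed article may also leave details of how the decision is elicited to the full protocol.

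All of this stands and narrows the point. It does not remove it. The article fixes the eligibility rule without exception, does not restrict the decision to repeat or on-time screening, and states a population-wide model. Those statements do not fit together, and more detail on elicitation would not add the missing women.

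**Conclusion.** The point holds as a mismatch between sample and claim. The focus groups cannot show or test what stops never-screened women or those lapsed for more than five years, so the population-wide EDM is not supported. The documents do not give the size of the gap: the excluded share lies anywhere from 0% to 48%.

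A usable outcome remains. If participants mirror the quoted rates, 28.8% to 63.0% would have had no mammogram in the last year and 0% to 48.0% none in two years. These ranges rest on the unknown five-year rate and on the mirroring assumption; recruitment through a clinic and by posters may give a different mix.

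The defect is confined to the EDM component. Aims 1 to 3 concern experience, satisfaction and the survey, and the eligibility rule suits them. The change should be made because, uncorrected, it overstates what the models can tell a later intervention.

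**What to change.** - Define the modelled decision as recent versus overdue screening: for example, last mammogram within 12 (or 24) months versus longer ago, up to five years. The 12-month cut is safer, because it leaves women on both sides over the whole range worked out above.
- Record the date of the last mammogram in the brief recruitment questionnaire that already assigns women to groups.
- Replace the population claim with a statement that the models describe repeat or on-time screening among AI/AN women screened within the past five years.

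The cost is one question and some rewording; eligibility, the number of groups and the satisfaction analyses stay as they are. The downside is that the models no longer claim to address first-time or long-lapsed screening.

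If the investigators want that question answered, women unscreened for five years would have to be recruited for the EDM work. Reserving one of the three groups in each stratum would keep the total at 12 but leave two per stratum, 8 of 12, for the satisfaction themes that feed Aim 1 and the survey. That is a real trade-off against the main aims and is not needed to correct the claim.
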